## Abstract

**Background:**

Knee osteoarthritis (KOA) is a prevalent degenerative joint disease that is characterized by joint pain, stiffness, and dysfunctional impairment, imposing a substantial medical burden annually. Tuina, a widely used noninvasive traditional Chinese medicine therapy commonly used for KOA, has been used for the management of this condition; however, its additive benefit to acupuncture remains unclear.

**Objective:**

The objective of the study is to assess whether the effectiveness of acupuncture-combined Tuina is superior to that of acupuncture in the management of KOA.

**Methods:**

This single-center, parallel-group, randomized controlled trial aims to enroll 60 patients with KOA, who will be randomly assigned to either a Tuina group (acupuncture-combined Tuina) or an acupuncture group (30 patients per group). Baseline assessments will include demographic and clinical evaluations: the visual analog scale from the short-form McGill Pain Questionnaire, pain threshold, muscle tension, 10-meter walking test, Western Ontario and McMaster Universities Osteoarthritis Index, and multimodal magnetic resonance imaging. Over a 6-week intervention, the Tuina group will receive Tuina on the basis of acupuncture, that is, acupuncture-combined Tuina, while the acupuncture group will undergo just acupuncture, with both groups continuing standard care as prescribed. Posttreatment, clinical outcomes and safety will be reassessed using baseline indicators. A 12-week follow-up will include all clinical evaluations. Assessments will be conducted by blinded assessors, and statistical analyses will be conducted by independent, blinded analysts. Outcomes will evaluate clinical pain and functional differences between groups and will elucidate the underlying cerebral mechanisms.

**Results:**

This study was funded in August 2024. The experimental plan will begin on December 31, 2025, and end on May 4, 2027.

**Conclusions:**

This trial aims to verify whether acupuncture-combined Tuina receives better efficacy than single acupuncture, as well as to explore the neuroimaging mechanisms that are clinically affected, thus providing scientific evidence for the treatment of clinical patients with KOA.

## Introduction

Knee osteoarthritis (KOA) is a prevalent and debilitating condition characterized by joint pain, stiffness, and restricted mobility, significantly impairing daily functioning and work participation [1-3]. In the United Kingdom, employees with arthritis have a 1.35% higher rate of sickness absence than their counterparts without arthritis [4]. The prevalence of KOA is 8.1% in China and 12.1% in the United States and Europe, with rates expected to rise as global populations age [5,6]. Currently, there is no treatment that can completely stop or reverse the progression of osteoarthritis [7,8]. Due to painfulness from the knee joint, patients usually use painkillers, but there is a risk of overuse and side effects of analgesic drugs [7-9]. The effectiveness of acupuncture in treating KOA in improving pain has been preliminarily verified [10,11]. Tuina, a traditional Chinese medicine manipulation therapy, is applied in the clinical treatment of KOA. However, whether the clinical efficacy of acupuncture-combined Tuina is more effective than single acupuncture remains to be proven.

Recent advances in neuroimaging, particularly the use of multimodal magnetic resonance imaging (multi-MRI), have provided powerful tools for investigating changes in brain activity involved in the pathogenesis of KOA, complementing research on biomechanics, aging, and genetic factors [12-14]. Pain, the hallmark symptom of KOA, results from complex interactions between brain regions responsible for pain transmission and modulation [15-17]. Emerging evidence suggests that KOA-associated pain is linked to functional activation and structural alterations in the cerebral cortex and subcortical regions [18,19]. Studies have identified increased resting-state functional connectivity between the ventrolateral periaqueductal gray and the bilateral thalamus in patients with KOA with knee pain compared to healthy controls [20]. Additionally, gray matter (GM) volume reductions in the bilateral insula and hippocampus have been observed [21]. Both static and dynamic functional network connectivity have been shown to correlate with clinical symptoms in KOA [22], highlighting the complex neural mechanisms underlying the condition.

Acupuncture, a core component of traditional Chinese medicine, is recommended in the Chinese Guidelines for Diagnosis and Treatment of Osteoarthritis (2024 Edition) as an effective treatment for alleviating pain and improving joint function in patients with KOA [23]. Studies have demonstrated that acupuncture effectively reduces joint pain and enhances functionality [24,25], with its therapeutic benefits lasting up to 4.5 months compared to sham acupuncture [26]. Evidence suggests [27-30] that acupuncture alleviates KOA by modulating central neural pathways, with its mechanisms varying based on the treatment modality and patient pathology, as reflected in specific cerebral alterations and activation patterns.

Tuina, a noninvasive Chinese therapeutic massage, is widely used for managing KOA due to its direct effects on the musculoskeletal system [31]. Through techniques such as pressing and kneading, Tuina alleviates pain and stiffness, while also improving knee stability, muscle strength, and joint mechanics, thus supporting long-term recovery [23]. Unlike acupuncture, which focuses on neurophysiological pathways, Tuina emphasizes physical manipulation of the musculoskeletal system to address knee joint dysfunction and muscle tension, enhancing joint stability and optimizing movement patterns [32,33]. The process of Tuina tends to be more acceptable to patients, as it is tender, comfortable, and associated with no injury, which is able to effectively relieve the pain, negative emotion, and dysfunction in patients with KOA.

As a result, to compare whether acupuncture-combined Tuina is better than single acupuncture, as well as to reveal the mechanism of analgesic effect that acupuncture-combined Tuina imposes to the brain center, an optimal, efficient, randomized comparative trial will be carried out, aiming to provide more scientific evidence for treating patients with KOA clinically.

## Methods

### Design

This is a single-center, parallel, randomized controlled trial. On the basis of the criteria established by the American College of Rheumatology [34], a total of 60 participants diagnosed with KOA will be recruited as eligible participants. These participants will be randomly assigned to 2 groups, each consisting of 30 individuals: the Tuina group (acupuncture-combined Tuina) and the acupuncture group. The intervention duration for both groups will be 30 minutes, administered 2 times weekly. The treatment period will last for 6 weeks, followed by a 12-week follow-up period.

Outcome measurements and magnetic resonance imaging scans will be assessed at baseline and at 6 weeks posttreatment, followed by a 12-week clinical follow-up period. Once data collection is completed, analyses will be conducted to evaluate changes in clinical indices and cerebral multi-MRI parameters across groups. The trial flowchart and study schedule for data collection are illustrated in Figure 1 and Table 1, respectively.

**Figure 1. F1:**
[figure not shown]
Flowchart of the trial. This study is a randomized controlled trial using multimodal magnetic resonance imaging (multi-MRI) and plans to enroll 60 patients with knee osteoarthritis. These patients will be equally allocated to 2 groups: the Tuina group and the acupuncture group, with 30 patients in each group. The trial will include a 6-week treatment period. During the treatment, patients in the Tuina group will receive 12 Tuina sessions based on acupuncture, whereas those in the acupuncture group will only receive acupuncture. Outcome assessments and multi-MRI scans will be conducted at 2 time points: baseline and the end of the treatment (6 weeks later). Subsequently, only clinical outcomes will be evaluated during the 12-week follow-up period.

**Table 1. T1:** Study schedule for data collection^a^.

Period	−2 weeks	0 weeks	0‐6 weeks	6 weeks	6‐18 weeks	18 weeks
	Screening	Baseline	Intervention	Assessing	Follow-up	Assessing
Enrollment						
Eligibility	✓^b^					
Demography	✓					
Informed consent	✓					
Sign the informed consent		✓				
Medical history	✓		✓	✓	✓	✓
Physical examination	✓		✓	✓	✓	✓
Randomization		✓				
Interventions						
Tuina group (n=30)			✓			
Acupuncture group (n=30)			✓			
Assessments						
VAS^c^	✓	✓		✓		✓
SF-MPQ^d^	✓	✓		✓		✓
Pain threshold		✓		✓		✓
Muscle tension		✓		✓		✓
10MWT^e^		✓		✓		✓
WOMAC^f^		✓		✓		✓
Clinical efficacy				✓		✓
Multi-MRI^g^		✓		✓		
Trial evaluation						
Patients’ compliance				✓		✓
Safety evaluation				✓		✓
Credibility test				✓		✓
Adverse events				✓		✓
Analysis		✓	✓	✓	✓	✓

a The informed consent and examination will be conducted after recruitment. Then, matched patients with knee osteoarthritis will be randomized into 2 groups and receive treatment. Both clinical outcomes and multimodal magnetic resonance imaging scans will be performed at 2 time points. Only clinical data will be collected at the 12-week follow-up subsequently. Adverse events will be recorded in the case report form at any time during the study.

b ✓: used to indicate that the inspection item needs to be executed at the corresponding time point.

c VAS: visual analog scale.

d SF-MPQ: short-form McGill Pain Questionnaire.

e 10MWT: 10-meter walking test.

f WOMAC: the Western Ontario and McMaster Universities Osteoarthritis Index.

g Multi-MRI: multimodal magnetic resonance imaging.

### Participants

All patients will be recruited from the Qingpu Traditional Chinese Medicine Hospital, Shanghai, through a combination of posters, online announcements, and promotional pamphlets. The inclusion and exclusion criteria for participants are presented in Textbox 1.

Textbox 1.The inclusion and exclusion criteria for participants.Inclusion criteriaMeet the diagnostic criteria for knee osteoarthritis set by the American College of Rheumatology [34].Be aged between 40 and 70 years, with left knee pain mainly or left knee pain only, as well as right-hand dominance.Have a Kellgren-Lawrence radiological [35] grade of I-II.Present with a visual analog scale score >3 from the short-form McGill Pain Questionnaire and a disease duration of at least 3 mo.Voluntarily agree to participate in this study and sign the informed consent form.Exclusion criteriaHave a history of trauma or knee surgery.Have tumors, tuberculosis, osteomyelitis, or other diseases affecting the knee.Exhibit severe hepatic or renal dysfunction, severe cardiovascular diseases, diabetes mellitus, or mental illnesses that may interfere with the treatment of Tuina.Experience pain in the knee area or throughout the body due to other diseases.Have magnetic resonance imaging (MRI) contraindications, such as claustrophobia, pacemakers, defibrillators, heart stents, or intrauterine devices or any other conditions that prevent safe MRI scanning.Have skin lesions in the periarticular area of the knee joint.

### Sample Size Calculation

This study is designed as a superiority trial, with the sample size calculated using PASS 15 (NCSS, LLC). On the basis of relevant literature, a 2-point difference on the visual analog scale (VAS) score was defined as the superiority margin [36]. According to our preliminary experiments, the mean difference between the acupuncture group and the Tuina group (acupuncture-combined Tuina) is 3.25, with an SD of 1.5 in both groups. Using a superiority test with an *α* of .025 and a power of 0.8, and accounting for a 20% dropout rate, the calculated sample size is 30 cases per group, resulting in a total of 60 cases required.

### Randomization and Allocation Concealment

This study uses blocked randomization to ensure unbiased group allocation. The statistical software SPSS 21.0 will be used to randomly assign participants to either the Tuina group or the acupuncture group. The randomization process will be performed by an independent statistician who will generate 60 random numbers of varying sizes using a computer. This statistician will have no involvement in participant recruitment, assessment, treatment administration, or data analysis, ensuring the independence and impartiality of the process.

Participants will be sequentially numbered from 1 to 60, and blocked randomization will be applied with a block size of 4. Within each block, treatment allocation (Tuina or acupuncture) will be determined by computer-generated random numbers, with smaller numbers assigned to Tuina and larger numbers assigned to acupuncture. The allocation process within each block will be dynamic and unpredictable, ensuring an equal distribution of participants between the 2 groups in a 1:1 ratio.

To ensure allocation concealment, the randomization scheme will be enclosed in opaque, sealed envelopes, numbered sequentially according to participant enrollment. Each envelope will contain the allocation result for the corresponding participant, whereas the outside will remain blank to prevent unintentional disclosure. These envelopes will remain sealed until the treatment allocation is determined, and they will be stored securely to prevent premature access to the allocation information. The assigned treatment (acupuncture-combined Tuina group or the acupuncture group) will be revealed only by opening the envelope corresponding to the participant’s number, ensuring the integrity of allocation concealment and enhancing the scientific rigor of the study.

### Blinding

This clinical trial will implement blinding for assessment to minimize potential biases. Statistical analysts will be blinded to participant recruitment, allocation, and treatment details to ensure the integrity and reliability of the study results. They will not have access to raw data until after the data collection process is completed and quality control measures are in place.

Due to the nature of Tuina and acupuncture interventions, achieving full blinding of patients and therapists is not feasible [37]. To minimize potential bias, therapists will not be involved in participant information collection, assessment, or subsequent data analysis. They will also refrain from disclosing information regarding the specific benefits or risks of the treatments to patients [38]. Additionally, to mitigate bias, outcome assessors and statisticians will remain blinded to group allocation throughout the study.

### Interventions

#### Overview

Participants in this study will receive a total of 12 treatment sessions over a 6-week period. The interventions will be administered by therapists with at least 6 years of professional experience in Tuina and acupuncture. All therapists will undergo standardized training to ensure consistency in treatment delivery, focusing on session duration, target treatment areas, and the specific techniques used.

To maintain the study’s integrity, patients will be prohibited from using concomitant medications or receiving alternative interventions during the treatment period. Celecoxib (Pfizer) will be allowed for pain management, but only if necessary and not within 48 hours before outcome measurements. During the follow-up phase, any medication use or additional interventions will be documented thoroughly to ensure an accurate assessment of the effects of Tuina and acupuncture, thereby isolating their impact on patient outcomes. This approach will guarantee the validity and reliability of the study findings.

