### Follow-Up

Upon completion of the 6-week intervention period, all patients will immediately transition into a 12-week unsupervised follow-up phase. At the end of the 18-week clinical period, patients with KOA will undergo assessments for all clinical evaluations, with the exception of except for the multi-MRI outcomes.

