#### Primary Outcomes

The VAS score is based on a 10-cm long straight line, with the starting end marked as 0 points, indicating no pain, and the end marked as 10 points, indicating unbearable severe pain. Patients will select a point on the line that represents their current level of pain. A lower total score indicates reduced pain severity, reflecting the effectiveness of the interventions. This VAS is distinct from the VAS component within the short-form McGill Pain Questionnaire (SF-MPQ), which is used solely for screening purposes and for baseline characterization.

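### The 48-hour pre-visit rule names only celecoxib, so the week-18 VAS can be taken under another recent analgesic

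*Protocol article*

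**What the plan says.** The medication rules stand in the Protocol article under Methods, Interventions, Overview. Patients are "prohibited from using concomitant medications or receiving alternative interventions during the treatment period". One drug is excepted: "Celecoxib (Pfizer) will be allowed for pain management, but only if necessary and not within 48 hours before outcome measurements". In follow-up nothing is banned; any medication or additional intervention "will be documented thoroughly to ensure an accurate assessment of the effects of Tuina and acupuncture, thereby isolating their impact on patient outcomes". The paragraph ends: "This approach will guarantee the validity and reliability of the study findings".

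Under Follow-Up, after week 6 "all patients will immediately transition into a 12-week unsupervised follow-up phase". Under Primary Outcomes, the VAS is a momentary rating: "Patients will select a point on the line that represents their current level of pain". Table 1 schedules it at week 18 as well as at baseline and week 6. Statistical Analysis puts all three readings into a linear mixed model whose key test is the group-by-time interaction.

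The Methods paragraph of the Abstract says that both groups keep their prescribed standard care, and it gives no exception.

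**The concern.** The plan evidently regards a recent analgesic dose as something to keep out of the outcome readings, since it imposes a 48-hour gap for celecoxib. Naming one drug is enough while every other drug is banned. Once that ban lapses, the gap still covers one drug and the rest are unrestricted.

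A rating of present pain responds to a recent dose, so the week-18 value could mix what remains of the treatment effect with a drug effect on the day. If recent use were equal in the two arms, the contrast would not move. It could be unequal: the Introduction says that "patients usually use painkillers, but there is a risk of overuse and side effects of analgesic drugs", and the Blinding section says that "achieving full blinding of patients and therapists is not feasible". That makes differential use plausible but does not show it.

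At stake is the meaning of the week-18 comparison, on which the Discussion relies for long-term effects. A pre-visit restriction is a conduct rule. Recorded use can support sensitivity analyses, but no analysis can recover an analgesic-free reading that was never taken.

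**Working it through.** **Rules by period**

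| Period and visit | Celecoxib | Other analgesics |
|---|---|---|
| Weeks 0-6, week-6 visit | Allowed if needed, not in the last 48 h | Banned (Interventions overview) |
| Weeks 6-18, week-18 visit | Not in the last 48 h, if the clause is read to reach this visit | Recorded only; no pre-visit limit |

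At week 6 the ban and the 48-hour clause together cover every analgesic. At week 18, even on the generous reading of the clause, only celecoxib is covered. If the Abstract's statement governed weeks 0-6 instead, the same gap would also reach week 6.

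**The plan's own figure, as context.** Sample Size Calculation gives a difference of 3.25, a margin of 2, SD 1.5, alpha .025, power 0.8 and 20% dropout. With a distance from the margin of 3.25 - 2 = 1.25 and one-sided alpha .025, the t-based size is 24 per arm, and 24 / (1 - 0.20) = 30 per arm. The stated size reproduces, and the fix below does not change it.

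**Size of a possible shift.** The documents give no uptake and no drug effect, so these inputs are assumptions: drug effect *e* = 0.5 to 1.5 VAS points, and net between-arm difference in recent use *d* = 10% to 40%. Shift = *e* × *d*.

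Precision with 24 per arm: SE = 1.5 × √(2/24) = 0.433; t(46, .975) = 2.013; 95% half-width = 0.433 × 2.013 = 0.872.

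| *e* | *d* | Shift | Share of 3.25 | Share of half-width |
|---|---|---|---|---|
| 0.5 | 10% | 0.05 | 1.5% | 5.7% |
| 1.0 | 20% | 0.20 | 6.2% | 22.9% |
| 1.5 | 40% | 0.60 | 18.5% | 68.8% |

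The sign is open. More use in the acupuncture arm would shrink the difference, and more use in the Tuina arm would enlarge it.

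**How much differential use matters.** A shift of 0.5 points needs a use difference of 0.5/1.5 = 33%, 0.5/1.0 = 50%, or 0.5/0.5 = 100%.

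**Effect on detection.** At 3.25 - 0.60 = 2.65, noncentral-t power against zero with 24 per arm is above 0.999, at two-sided .05 and also at a Bonferroni .025.

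**What the rule would achieve.** If a quarter of the drug effect remained after 48 hours, or non-adherence left that much, 0.60 would fall to 0.25 × 0.60 = 0.15. The rule reduces the shift without necessarily removing it.

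**The case against.** *The gap is narrow, and an article leaves visit instructions to the full protocol.* The first half stands: the gap is one visit and drugs other than celecoxib. The word unsupervised describes the 12 weeks, and it does not show that patients get no instruction before the visit. However, the article does not leave the rule out. It states the rule and limits it to one named drug, so the point concerns what is written.

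*Under intention to treat in a self-described pragmatic trial, later analgesics are part of the strategy.* That comparison is legitimate, and nothing here calls it invalid. A pre-visit restriction is compatible with it, and the plan has already chosen one for celecoxib. Extending it to equivalent drugs makes that choice consistent. It would not deal with the additional interventions that follow-up also permits.

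*Baseline use cannot depend on the arm.* This stands. Use before randomization is balanced in expectation and creates no systematic bias between arms. Including baseline serves consistent measurement only.

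*The size is entirely assumed.* This also stands. The 0.60 figure needs the largest assumed effect and the largest assumed use gap together.

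A reader might infer that power collapses. Against the 2-point margin, a 0.60 adverse shift would cut power from about 82% to 32% (normal approximation, 24 per arm). The documents do not support that as a finding: the inputs are assumed, the sample size section ties the margin to no visit, and the planned test is a group-by-time interaction.

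**Conclusion.** The point holds as a limited defect in a stated conduct rule. As written, the week-18 VAS may be taken under a recent analgesic other than celecoxib, and that reading enters the primary model. On the assumed ranges the shift is 0.05 to 0.60 points in either direction. Neither its size nor its sign can be derived from the documents, the low end is negligible, and detection of the planned difference from zero is not threatened.

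Two stronger readings should be resisted. One is that the week-18 contrast is biased: that needs differential use, which is plausible but undocumented. The other is that the week-6 contrast is compromised: it is unaffected if the treatment-period ban governs. The Abstract contradicts that ban, so the text needs to say which rule applies in weeks 0-6.

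The claim that documenting follow-up medication isolates the treatment effects is a minor wording error. Recording use after randomization does not separate its effect from that of treatment.

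**What to change.** 1. State in the Interventions overview that no rescue or short-acting analgesic, celecoxib or other, is to be taken within 48 hours before the week-6 and week-18 assessments. Apply the same rule at baseline for consistent measurement only. Record any breach.
2. Make the Abstract's statement on standard care agree with the treatment-period ban, so that one co-treatment rule governs weeks 0-6.
3. As a minor edit, drop the claims that documentation isolates the effects and guarantees validity. Say instead that week 18 compares the assigned strategies including later care.

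The cost is a few sentences and one visit instruction. The Results section says recruitment is not yet open, so every participant can be covered. The downside is up to 48 hours without analgesics before visits, which the plan already asks of celecoxib users, and a more modest long-term claim. The sample size does not change.
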